#### Data Analysis by Aim

We describe the planned analyses by aim.

Before analyses, data will be audited for quality and completeness. Descriptive statistics will be calculated, and variable distributions will be evaluated to ensure they meet the assumptions of planned analytic models, including detection of outliers. In this study, *t* tests and chi-square analyses will be used to assess group equivalence at baseline. Variables showing differences across the 4 groups will be considered for inclusion as covariates in the analyses. All analyses will be conducted using SAS (SAS Institute) or R (R Foundation) software, with statistical significance set at an α level of .05.

Aim 1 analyses will follow an intention-to-treat approach. Random-effects logistic regression will be used with PrEP uptake as the primary outcome. The model will include time (baseline, 6, 12, and 18 months), a categorical variable for study condition (PrEP4T, LS4TM, PrEP4T + LS4TM, with SOC as the reference), and the time × study condition interaction to test whether changes in PrEP uptake over time differ across the 3 intervention conditions compared with SOC. Baseline characteristics that differ across study conditions, as well as variables related to missingness, will be included as covariates if necessary. The primary parameter of interest is the time × study condition interaction term; a significant interaction would indicate that the rate of PrEP uptake over time differs between the intervention and SOC groups. Significant interactions will be graphed and interpreted. We hypothesize that PrEP uptake will be highest among participants randomized to condition D (PrEP4T + LS4TM). The same analytic approach will be applied to the secondary outcome of PrEP adherence. PrEP persistence will be assessed at months 12 and 18 using random-effects logistic regression, including time (12 and 18 months), study condition, and the time × study condition interaction. HIV and sexually transmitted infection incidence will be evaluated using logistic regression, with incidence between baseline and 18 months as the outcome and study condition as the predictor.

Aim 2 will use causal inference methods from epidemiology [96,97] to conduct mediation analyses and examine the mechanisms of action for the interventions. Mediation analyses will estimate the natural direct and indirect effects of proposed mediators—health care empowerment, TMSM community connectedness, and IMB constructs—on the relationship between intervention condition and PrEP uptake compared with SOC. Mediation models will be implemented using a series of random-effects logistic regression models, consistent with the approach described in aim 1.

For aims 1 and 2, patterns of missingness will be examined, and baseline responses will be compared between participants with and without missing data. Variables associated with missingness will be included in the analyses to yield valid inferences [98]. Modern missing data techniques [99] will be employed, with multiple imputation used to handle missing data, including participants lost to follow-up [100]. Sensitivity analyses will compare parameter estimates from completer-only analyses with those from multiple imputation to assess potential bias.

Aim 3 qualitative data from IDIs will be analyzed to explore PrEP decision-making and participant experiences with the interventions. An iterative analytic process will follow Crabtree and Miller’s [101] 5-step approach: (1) describing, (2) organizing, (3) connecting, (4) corroborating, and (5) representing. Regular debriefing meetings with data collectors will identify preliminary findings and guide iterative data collection and analysis. An initial set of codes will be developed based on the study’s conceptual frameworks of Healthcare Access, Gender Affirmation, and IMB constructs. Qualitative codes will be applied to transcripts and interview notes using qualitative analysis software by 2 independent analysts. New codes will be added as themes emerge. Summaries will be created for major themes and differences across subgroups. Descriptive quantitative survey data (eg, demographics, social and medical gender affirmation) may be used to contextualize qualitative findings. CAB members will provide ongoing input and help corroborate the qualitative results.

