### Randomization and Blinding

Participants were randomized after their baseline HIV results were received and confirmed. Randomization was automated, computer-generated, and allocation sequences were concealed. Stratification was based on ethnoracial identity (BIPOC or Latine vs White) and MAP state LGBTQ equality policy tally (“high, medium, or fair” vs “low or negative” overall policy tally, as of October 2023; see Table S2 in Multimedia Appendix 1) [55]. The MAP state LGBTQ equality policy tally assesses over 50 LGBTQ-related laws and policies across US states (eg, nondiscrimination, health care access, religious exemptions, identity documents), providing a snapshot of the legal and policy climate for LGBTQ people [55]. Stratification was implemented to ensure balance across study arms and to facilitate subgroup analyses [88], given the disproportionate HIV burden among BIPOC or Latine versus White individuals [5] and the impact of repressive anti-LGBTQ policies on HIV prevention efforts [89]. Blinding was maintained at the statistician and investigator levels [90], but was not possible for participants or intervention staff.

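### The Aim 1 model leaves out both randomization stratification factors and picks covariates by baseline tests and missingness, so the primary model is not fixed in advance

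*Protocol article*

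**What the plan says.** The Randomization and Blinding section of the protocol article states: "Stratification was based on ethnoracial identity (BIPOC or Latine vs White) and MAP state LGBTQ equality policy tally". It gives the purpose as well: "Stratification was implemented to ensure balance across study arms and to facilitate subgroup analyses". It justifies the two factors by unequal HIV burden and by the effect of hostile state policy on HIV prevention, so the authors regard both as relevant to the outcome.

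Data Analysis by Aim specifies a logistic model with random effects for PrEP uptake. On its terms it says: "The model will include time (baseline, 6, 12, and 18 months), a categorical variable for study condition". To these it adds the product of time and condition, and it then singles that product out as the test that matters: "The primary parameter of interest is the time × study condition interaction term". Neither stratification factor is named as a model term there or elsewhere in the analysis section.

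The same section gives a rule for other covariates. Baseline equivalence of the arms is assessed with t tests and chi-square tests, and then: "Variables showing differences across the 4 groups will be considered for inclusion as covariates in the analyses". For the Aim 1 model it adds: "Baseline characteristics that differ across study conditions, as well as variables related to missingness, will be included as covariates if necessary". The mediation models of Aim 2 follow the Aim 1 approach. The logistic model for HIV and STI incidence names study condition as its predictor and nothing else.

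**The concern.** Three things go wrong when the rule and the design are read together.

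- **The rule works against the stratification.** It looks for imbalance, and stratified allocation removes imbalance in exactly these two factors. The variables with the best claim to be in the model are the ones it will not find.
- **The rule selects on chance.** After concealed randomization, a baseline difference between arms is a chance difference. A significance test of it says nothing about whether the variable predicts PrEP uptake, which is what decides whether adjustment is useful.
- **The primary model stays open.** No covariate list or threshold is given, and entry is left to later judgement. Which variables relate to missingness can be known only once follow-up data have accrued. In a logistic model the choice also affects what is estimated: odds ratios are non-collapsible, so adding or dropping a prognostic covariate changes the conditional odds ratio being targeted, not only its precision.

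At stake are the reproducibility of the primary estimate and some power in the simpler contrasts. The matter is sharper because 103 participants had been enrolled when the award was terminated, against a target of 300. That is 103/4 ≈ 26 per arm if allocation was equal. Chance imbalances are larger at that size, and ad hoc covariates are harder to support.

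**Working it through.** The plan gives no figure of its own on covariate adjustment, and its power statement names no covariate, so there is nothing to reproduce first.

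**Inputs from the article:** two binary stratification factors (four strata), 1:1:1:1 allocation, 300 participants (75 per arm), α = .05, a random-effects logistic model with time points at baseline, 6, 12 and 18 months, and the time × condition interaction as primary parameter.

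**Assumptions, not in the article:** two-sided testing; permuted blocks of four within strata; how strongly the strata predict uptake (log odds ratios varied); random-intercept SD of 1.5; time as a linear term, so that the interaction has 3 degrees of freedom; the number of baseline variables tested, and their independence.

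**Step 1. Can the rule select a stratification factor?** Allocation was simulated for 300 participants, with stratum shares of 50% and 40%. Each factor was compared across the four arms by chi-square test at .05. In 3,000 trials × 2 factors = 6,000 checks, none was flagged.

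**Step 2. How often does chance flag something else?** P(at least one flagged) = 1 − 0.95^k.

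- k = 10: 1 − 0.95^10 = 40%
- k = 20: 1 − 0.95^20 = 64%
- k = 30: 1 − 0.95^30 = 79%

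The article does not say how many variables will be tested. Its Assessments and Survey Measures section names nine demographic items alone, before the behavioral and psychosocial scales. These are probabilities of being flagged. Flagged variables are only considered for entry, so the chance that one enters the model is not known.

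**Step 3. Primary test: rejection rate with no true effect, nominal 5%.**

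| Stratum log odds ratio: level, slope | Runs | Strata omitted | Strata included |
|---|---|---|---|
| 0.5, 0.2 | 2,400 | 5.3% | 5.3% |
| 1.0, 0 | 1,200 | 5.0% | 4.8% |
| 1.0, 0.4 | 1,200 | 4.8% | 5.3% |

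The simulation standard error is about 0.4 to 0.6 percentage points, so no difference is detectable.

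**Step 4. Single-time-point arm contrast (75 per arm, logistic, Wald test, 3,000 runs per row), no true effect.**

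| Stratum log odds ratio | Strata omitted | Strata included |
|---|---|---|
| 0 | 4.7% | 4.8% |
| 0.5 | 4.8% | 5.1% |
| 1.0 | 4.3% | 5.3% |
| 1.5 | 3.2% | 4.7% |

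The simulation standard error is √(0.05 × 0.95/3,000) ≈ 0.4 points. Omitting strongly prognostic strata makes the test conservative. A weak stratum effect makes no visible difference.

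**Step 5. Does selection by baseline test inflate the error?** In the Step 4 setting, a prognostic covariate was added only when its baseline test was significant. Rejection rates ran from 2.9% to 4.5% across the four rows, so there was no inflation.

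**The case against.** **A full covariate list is normally left to the SAP, and saying what a model will include does not exclude other terms.** If the article had been silent, this would end the matter. It is not silent: it publishes a selection rule, and a SAP with a fixed list would have to depart from it. The planned subgroup analyses give the strata a use, but not a place in the primary model.

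**Statistician and investigator are blinded, and baseline selection does not use outcomes by arm.** This is true and reduces the scope for steering the result. It does not turn a rule driven by chance imbalance into a pre-specified model.

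**Multiple imputation is planned, with a comparison against completers.** This deals with much of the missingness concern. What remains is the provision to put predictors of missingness into the outcome model as the need is judged.

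**A reader might infer that omitting the strata miscalibrates the primary test.** The textbook formula for a linear, single-time-point contrast, 2·(1 − Φ(1.96/√(1 − R²))), gives a true size of 4.4% at R² = .05 and 3.9% at R² = .10, with standard errors 2.6% and 5.4% too wide (1/√(1 − R²)). Those R² values are assumed, and the formula does not describe a time × condition interaction in a random-effects logistic model, where the random intercept absorbs most of a participant-level stratum effect. Step 3 shows no detectable miscalibration. The documents do not support this stronger reading.

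**Conclusion.** The point holds as a matter of pre-specification and consistency with the design. The stated rule will in practice pass over the two stratification factors, has a 40% to 79% chance of flagging at least one variable by chance alone (10 to 30 independent variables, assumed), and leaves the primary model and its conditional odds ratio dependent on the data. The size of any shift in that odds ratio was not computed.

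The type I error of the primary time × condition test is not materially affected. For level or single-time-point contrasts, HIV and STI incidence being the clearest case, omission makes tests conservative: 4.3% at a stratum log odds ratio of 1.0 and 3.2% at 1.5, and negligible at 0.5. That is some loss of power, not false positives. The article does not say how prognostic the strata are, so the actual loss is unknown. The simulations are for 300 participants and were not repeated for 103.

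**What to change.** 1. Name both stratification factors, coded as in the allocation system, as covariates in the Aim 1 and Aim 2 models. Do the same in the HIV and STI incidence model if there are enough events to support them.
2. Drop baseline significance testing as a way of choosing covariates, and describe baseline characteristics by arm only. Any further covariate should be named in advance because it is expected to predict the outcome.
3. Use predictors of missingness as auxiliary variables in the multiple imputation already planned, not as ad hoc covariates in the outcome model.
4. Do not add baseline PrEP status from dried blood spots as a covariate in the uptake model. Baseline is already a modelled time point there, and drug levels were assayed only in participants who reported recent PrEP use.

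The cost is a change of wording. Both factors are known at randomization, and neither sample size nor data collection changes. The one small downside is that the reported odds ratios become conditional on the strata, which the report should state.

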### Study Objective and Aims

The goal of the Transmasculine One-on-One and Group Empowerment for Targeted HIV Reduction (TOGETHR) study was to evaluate the effectiveness of digitally delivered individual and small-group peer-based strategies in improving PrEP uptake and adherence among at-risk, HIV-negative adult TMSM.

Applying the Healthcare Access [49], Gender Affirmation [7,51], and IMB [53] frameworks, we conducted a digital, open-label, randomized 2×2 factorial trial (1:1:1:1 allocation) of peer-delivered HIV prevention strategies to increase PrEP uptake among TMSM (n=300) residing in Ending the HIV Epidemic (EHE)–prioritized geographic hot spots in the United States. The specific aims were to:

Aim 1. Compare the efficacy of 4 peer-delivered HIV prevention strategies implemented over 6 weeks to increase PrEP uptake (primary outcome) among 300 PrEP-indicated, HIV-negative TMSM, which include(A) standard of care (SOC)digital PrEP locator and a library of syndicated HIV prevention, sexual health, and antistigma materials;(B) SOC + PrEP for transgender men and transmasculine people (PrEP4T; 1-on-1 PrEP peer navigation); (C) SOC + LifeSkills for Transgender Men and Transmasculine People (LS4TM; peer-delivered group-based PrEP behavioral intervention); or (D) SOC + PrEP4T + LS4TM.Hypothesis 1.1:Rates of PrEP uptake will be higher in (B) SOC + PrEP4T and (C) SOC + LS4TM conditions compared with (A) SOC (main effects).Hypothesis 1.2:PrEP uptake rates will be highest for participants randomized to (D) SOC + PrEP4T + LS4TM compared with (A) SOC (additive effects).Aim 2. Examine the mechanisms through which PrEP4T and LS4TM impact PrEP uptake using causal mediation analysis.Hypothesis 2.1:Health care access empowerment, transgender community support for gender affirmation, and IMB constructs will mediate the relationship between PrEP4T, LS4TM, and PrEP uptake.Aim 3. Explore PrEP decision-making processes and intervention experiences through in-depth interviews (IDIs; n=40; 10 per condition) to inform future scale-up and implementation of these interventions.

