## Methods

### Study Design

The TOGETHR study was a collaboration between the University of Michigan and The Fenway Institute at Fenway Health. The Fenway Institute led study management, including recruitment and retention, enrollment, intervention implementation, and data collection. The University of Michigan was responsible for data analysis. Investigators from Johns Hopkins University, Duke University, Drexel University, and the University of California, Los Angeles also contributed to the study.

TOGETHR was a digitally delivered, open-label, randomized 2×2 factorial trial of peer-delivered HIV prevention strategies. The design included 2 factors: individualized 1-on-1 peer navigation (PrEP4T vs none) and group-based behavioral intervention (LS4TM vs none). The primary outcome was PrEP uptake, confirmed biologically. Secondary outcomes were PrEP adherence, defined as tenofovir diphosphate (TFV-DP) concentrations >700 fmol/punch (corresponding to >4 doses per week) [54], and PrEP persistence, defined as 2 consecutive dried blood spot (DBS) measures indicating PrEP use. Participants were randomized 1:1:1:1 to the 4 study conditions, with stratification by ethnoracial identity (Black, Indigenous, and People of Color [BIPOC] vs White non-Latine) and by Movement Advancement Project (MAP) state lesbian, gay, bisexual, transgender, and queer (LGBTQ) equality policy tally (“high, medium, or fair” vs “low or negative”) [55]. The enrollment target was approximately 50% BIPOC participants. The study protocol was developed in accordance with the 2025 Standard Protocol Items: Recommendations for Interventional Trials (SPIRIT) guidelines to ensure methodological rigor, transparency, and completeness in trial reporting [56].

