### Statistical Analysis

#### Power

Factorial trials can be powered to detect either main effects or interaction effects, depending on the anticipated influence of interactions within the trial context [92]. This trial was powered to detect the main effects of the PrEP4T and LS4TM interventions. The trial was not powered to detect a PrEP4T × LS4TM interaction effect because (1) based on our conceptualization, the interventions were distinct in delivery (individualized vs group based) and content (peer navigation vs. community support and IMB strategies), and informed by preliminary studies and knowledge of the study population, we did not anticipate a combined interaction effect; and (2) any potential interaction was expected to be negligible, described in factorial trials as a minor “small quantitative interaction” [92-94]. Both PrEP4T and LS4TM were distinct, peer-delivered digital interventions that TMSM endorsed for HIV prevention in our prior research. We hypothesized that each strategy would independently increase PrEP uptake by at least 20% among TMSM, addressing the main-effects research question. Although we did not anticipate interaction effects, we hypothesized additive effects such that participants assigned to the PrEP4T + LS4TM condition would achieve the highest PrEP uptake rates. These superiority hypotheses were supported by evidence from a systematic review of peer-delivered interventions [47].

We estimated PrEP uptake rates in the SOC condition based on prior TMSM data [8,15] and conducted simulations using an SAS macro [95]. Simulations varied the number of participants per condition (n=40-120) and the magnitude of intervention effects over 18 months (20%-40%) for the PrEP4T and LS4TM conditions. Assuming 10% attrition, a total sample size of 300 (75 per condition) provided 80% power or greater to detect a 20% increase in PrEP uptake for each intervention versus SOC at a .05 significance level. We selected a 20% increase because smaller differences were not considered clinically meaningful for potential scale-up. To account for attrition, we planned to enroll 375 participants at baseline, anticipating approximately 20% loss to follow-up, resulting in 300 participants completing the study.

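### Power is claimed for the two factorial main effects, but the primary contrasts named are single arms against SOC, and none of them tests whether the combination is best

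*Protocol article*

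**What the plan says.** The Study Design section sets out a 2×2 factorial: "The design included 2 factors: individualized 1-on-1 peer navigation (PrEP4T vs none) and group-based behavioral intervention (LS4TM vs none". Allocation is equal: "Participants were randomized 1:1:1:1 to the 4 study conditions".

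The Power section says "This trial was powered to detect the main effects of the PrEP4T and LS4TM interventions" and that "any potential interaction was expected to be negligible". Its sizing statement reads "Assuming 10% attrition, a total sample size of 300 (75 per condition) provided 80% power or greater", for a 20% increase in uptake for each intervention against SOC at the .05 level. It then plans to enrol 375 so that 300 complete. SOC uptake was estimated from earlier data, but the value is not given.

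Data Analysis by Aim specifies a random-effects logistic model with time, "a categorical variable for study condition (PrEP4T, LS4TM, PrEP4T + LS4TM, with SOC as the reference", and their interaction. That interaction is the primary parameter.

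Study Objective and Aims states Hypothesis 1.1 as "Rates of PrEP uptake will be higher in (B) SOC + PrEP4T and (C) SOC + LS4TM conditions compared with (A) SOC (main effects" and Hypothesis 1.2 as "PrEP uptake rates will be highest for participants randomized to (D) SOC + PrEP4T + LS4TM compared with (A) SOC (additive effects".

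**The concern.** In a 2×2 factorial with arms A (SOC), B (PrEP4T), C (LS4TM) and D (both), the main effect of PrEP4T compares B+D with A+C, and that of LS4TM compares C+D with A+B. Each uses all four arms. A four-level condition with SOC as reference yields B vs A, C vs A and D vs A, each using two arms. Hypothesis 1.1 calls B vs A and C vs A main effects, which they are not.

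The primary inference may therefore rest on contrasts with roughly 1.6 to 2 times the variance of those the design supports. The prediction that D is highest has no matching test either: D beating A says nothing about D against B or C.

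**Working it through.** **Inputs.** From the Power section: 75 per condition, 10% attrition, a 20% increase, α = .05; also 375 enrolled with 20% loss. Assumed: two-sided test, 20% meaning percentage points, additive cell rates p, p+.2, p+.2, p+.4, a single-time comparison, and SOC uptake p varied because it is not stated. A relative 20% increase was also tried. It gives only 6% to 21% (arm vs SOC) and 8% to 46% (main effect) for p from 10% to 50%, so it cannot be the basis of the 80%.

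**The plan's own figures.** 375 × 0.8 = 300 reproduces the enrolment target. The 80% cannot be uniquely reproduced without p. The two attrition statements give two analysed sizes: 300 × 0.9 / 4 = 67.5 per arm, or 375 × 0.8 / 4 = 75 per arm.

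**Arm versus SOC.** Power = Φ[(0.2√n − 1.96√(2p̄(1−p̄))) / √(p₁(1−p₁)+p₂(1−p₂))]. At p = 20%, n = 67.5: (1.643 − 1.270) / 0.632 = 0.590, so power is 72%.

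**Factorial main effect.** SE = ½√(Σ pᵢ(1−pᵢ)/n) over the four cells; power = Φ(0.2/SE − 1.96). At p = 20%, n = 67.5: ½√(0.88/67.5) = 0.0571, and 0.2/0.0571 − 1.96 = 1.54, so power is 94%. Pooling the margins (135 vs 135, pooled variance) gives 92%.

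| SOC uptake | Arm vs SOC, 67.5 per arm | Arm vs SOC, 75 per arm | Main effect, 67.5 per arm (two formulas) |
|---|---|---|---|
| 10% | 84% | 87% | 95–97% |
| 20% | 72% | 77% | 92–94% |
| 30% | 66% | 71% | 91–93% |

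Arm-versus-SOC power reaches 80% up to an SOC uptake of about 12% with 67.5 per arm, or about 16% with 75.

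**Variance ratio (arm vs SOC over main effect).** At p = 20%: (0.16+0.24)/67.5 = 0.00593 against 0.0571² = 0.00326, ratio 1.8. It is 1.6 at 10% and 2.0 at 30%.

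**Longitudinal illustration.** In 300 simulated trials per SOC rate (67 per arm, linear change to month 18, latent correlation 0.5, logistic GEE in place of the random-effects model), time × condition against time × factor gave 66% vs 77%, 56% vs 79% and 53% vs 84% at SOC uptake 10%, 20% and 30%. The direction is the same, but the main-effect levels are lower than in the table.

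**Is D best?** If B, C and D all equal p+.2, so that D adds nothing over either single intervention, D vs A is still significant 84%, 72% and 66% of the time at p = 10%, 20% and 30%. Under additivity, D vs B alone has about 65% to 66% power at those rates. Winning both D vs B and D vs C at 67.5 per arm has about 50% to 54% (unpooled variance, bivariate normal with the shared D arm; a point or two lower with pooled variance).

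**Scale.** Additive risks are not additive in logits. Cells .10/.30/.30/.50 have odds 0.111, 0.429, 0.429 and 1, so the interaction odds ratio is (1 × 0.111)/0.429² ≈ 0.60.

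**Multiplicity.** Three unadjusted comparisons with a shared control (null correlation 0.5) have a family-wise error of about 12.5% by simulation.

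**The case against.** Several stronger readings are tempting, and the document does not support them.

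- *Half the data are thrown away.* They are not. The four-level model fits every arm and is a reparameterised saturated factorial, so the main effects and D vs B or C are linear contrasts of the same fit. What is wrong is which contrasts are named as primary.
- *The analysis provably misses the quantity the trial was sized for.* The sizing sentence speaks of 75 per condition and each intervention against SOC. Read that way, it agrees with Hypothesis 1.1 and the model, and the error is the main-effects label. The Power section supports both readings, which is why it needs reconciling.
- *The trial is underpowered.* This is not shown. With SOC uptake of about 12% or less (16% with 75 per arm), the arm-versus-SOC contrast does reach 80%.
- *Family-wise error is 12.5%.* Only if three separate unadjusted tests are used. The text names one interaction term, which could be a joint test.

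It is also fair that a single-time calculation does not model the time × condition parameter, and that a logistic model with two factors and no product term is misspecified if risks are additive. Funding ended with 103 enrolled, which limits what any contrast can now show. None of this removes the conflict between the stated design and power basis and the stated primary parameter. Nor is that conflict a detail left to an analysis plan, since the article states the model, the reference level, the primary parameter and the hypotheses itself.

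**Conclusion.** The point holds as an inconsistency over the primary contrast. The design and the opening of the Power section describe main effects with negligible interaction; the model and Hypothesis 1.1 describe simple effects against SOC, and the hypothesis labels them main effects. Under the assumptions above, with 67.5 per arm, analysing by factor rather than by arm raises cross-sectional power from about 84%, 72% and 66% to 91–97% at SOC uptake of 10% to 30%. These sizes depend on an SOC rate that the article does not give. Hypothesis 1.2 as written cannot show that D is highest. The multiplicity point is secondary and conditional.

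**What to change.** - For Hypothesis 1.1, make the two factor × time effects (PrEP4T yes/no, LS4TM yes/no) primary, either as marginal contrasts from the four-cell model or with two 0/1 factors.
- Report the PrEP4T × LS4TM interaction with its confidence interval, and state the scale (risk difference or odds ratio) on which it is expected to be small.
- Keep the four cell rates and the arm-versus-SOC contrasts as supportive, and correct the main-effects label in Hypothesis 1.1.
- In the Power section, state which contrast the 80% refers to, the SOC uptake used, and the analysed number per arm.
- For Hypothesis 1.2, either drop the claim that D is highest, or add D vs B and D vs C as supportive contrasts and acknowledge only about 50% to 54% power to win both at 67.5 per arm.
- If the three SOC comparisons are kept as primary, say whether they are tested jointly or adjusted.

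The cost is wording and contrast definitions; no further data are needed. The downside is reliance on a small interaction, which the Power section already assumes. Deriving marginal contrasts from the four-cell model avoids having to leave the interaction term out.
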